##### Preliminary Psychometrics of Smart Track ROM Items

Preliminary psychometrics for Smart Track items will be explored via sensitivity to change, internal consistency, test-retest reliability, convergent validity, and exploratory factor analysis. Internal consistency of Smart Track ROM items will be evaluated using Cronbach alpha coefficient. Pearson correlation analysis will be used to examine the test-retest reliability of ROM scores for the first and second completion of each item set. Convergent validity will be examined using Pearson correlation analysis to explore the associations of initial ROM scores with the standardized measures (COMS and SURE) administered at baseline. Sensitivity to change will be examined via effect sizes, reliable change index (RCI), and growth curve modeling. As appropriate, internal consistency, test-retest reliability, concurrent validity, and RCI will be further examined as a function of age group, gender, and primary behavior of concern.

Effect sizes will be estimated for participants’ average ROM change scores between the first and last sessions. To explore the minimum reliable amount of change in scores (while accounting for measurement error [78]), we will calculate RCI between participants’ first and last ROM scores. The Jacobson and Traux criteria [78] will be applied to describe the proportion of participants who improved, did not change, or deteriorated. RCIs will also be calculated for the standardized measures administered at baseline and follow-up to allow comparisons with the ROM items. Growth curve modeling will be used to estimate the average rates of change in ROM scores across the 2-month period of ROM usage.

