### Overview of the mHealth Routine Outcome Monitoring and Feedback App (Smart Track)

The Smart Track app was designed for participants attending SMART Recovery groups. ROM items are intended for weekly completion. However, it is up to the individual to decide whether, when, and how they engage with Smart Track. Given the low-risk, low-burden nature of this study, there are no contingencies for discontinuing access to the Smart Track app. Owing to app store regulations, Smart Track will not be restricted to study participants. It will be freely available for download through Android and iPhone Operating System stores (only data from those who provide consent will be included in the study).

Publications detailing the methods and findings from the qualitative work [33] and app development process (including theoretical foundations) will be reported separately. To provide context, a brief summary is presented here. The Smart Track app was developed during the first phase of this study using participatory design workshops and an iterative development process informed by the (1) consideration of existing ROM tools, (2) qualitative feedback [33] and usability testing sessions with SMART Recovery participants and facilitators, (3) clinical and research expertise from the members of the expert advisory and steering committees, and (4) technological and creative expertise of the development team employed to work on this study (GHO, Sydney) [34].

The functionality of Smart Track was initially tested with 3 members of the research team. Several bugs were identified and fixed before the amended beta version was released to a convenience sample (n=40) for further testing. This convenience sample of beta testers included members of the expert advisory committee, steering committee, SMART Recovery board members, and SMART Recovery facilitators. Further refinements were made in line with the feedback received (bug fixes, minor amendments to functionality, and content).

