#### Implementation Strategies

The app contains an in-built *walk through* to orient new users to the features of the app. We also intend to develop a brief tutorial to assist participants with app download and set up. Consistent with the recommendations for improving ROM uptake [9], SMART Recovery facilitators at each study site will assume the role of *local champions* of Smart Track. The research team will work with the facilitators to orient them to the app so that they are confident in responding to the participants’ questions about ROM completion and troubleshooting any difficulties that may arise. Participants and facilitators may also contact the research team directly for support. SMART Recovery facilitators will also prompt, encourage, and support study participants to regularly complete the ROM questions before and/or attending a SMART Recovery group.

In-app push notifications will also be used to prompt participants to complete the ROM items. In-app notifications (red marker) will also be used to highlight section(s) that require participants’ attention (eg, outstanding 7-day plan).

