## Discussion

### Principal Findings

Integrating ROM and tailored feedback into SMART Recovery groups is an important step toward improving client care [5,6,79]. Given the dearth of published research specifically examining the effectiveness of SMART Recovery [27], ROM provides the opportunity to establish an evidence base for SMART Recovery. Improved engagement with ROM and feedback requires innovative solutions [9]. To overcome the current limitations [9,18,80], in this project, we have harnessed technology to develop a fee-free mHealth app that provides interactive, client-centered, multidimensional progress monitoring. Written and visual feedback is generated automatically and is available almost instantly. Consistent with the need to improve the quality of mHealth solutions [81], Smart Track is grounded in theory, informed by an in-depth understanding of the needs and opinions of SMART Recovery participants and facilitators, and will undergo methodologically rigorous evaluation.

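### Test-retest reliability is a Pearson correlation of completions paired by order rather than time, and first-to-last change scores cover spans set by each person's length of app use

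*Protocol article*

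**What the plan says.** The section on preliminary psychometrics of the Smart Track ROM items fixes both the statistic and the pairing: a Pearson correlation is to "examine the test-retest reliability of ROM scores for the first and second completion of each item set". It states no interval and no criterion that the person be stable.

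On timing, the overview of the app says "ROM items are intended for weekly completion", then adds that "it is up to the individual to decide whether, when, and how they engage with Smart Track". Under Implementation Strategies, "In-app push notifications will also be used to prompt participants to complete the ROM items", and facilitators prompt as well. Table 2 lists the ROM items as weekly. On what happens between completions, the Principal Findings section says: "Written and visual feedback is generated automatically and is available almost instantly". The section on tailored feedback describes its aims as reinforcing progress, pointing to further change, or troubleshooting.

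Sensitivity to change has three planned analyses in the psychometrics section. Effect sizes are for "average ROM change scores between the first and last sessions". For the reliable change index, "we will calculate RCI between participants’ first and last ROM scores". Growth curve models estimate average rates of change over the 2 months. RCIs are also to be computed for the interview measures at baseline and follow-up, for comparison with the ROM items. The reliability coefficient that enters the RCI is not named.

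**The concern.** A test-retest coefficient describes measurement error only if the thing measured is stable between occasions, or at least if the gap is short and similar for everyone. Here neither condition is set. The second completion may come a week after the first or several weeks later, and feedback intended to support change is shown in between.

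Pearson's r then has two weaknesses. It does not register a shift common to all users. It does register differences between people in true change, and counts them as unreliability, more so as gaps lengthen.

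For the first-to-last effect size and RCI the problem is different. Change is what these analyses aim to measure, so its presence is no fault. The difficulty is the span: one person's first and last completions may be a week apart and another's two months. The summary therefore depends partly on how long people kept using the app, and people with a single completion contribute nothing. The interview RCIs run over a scheduled 2 months. If the two sets of proportions improved, unchanged or deteriorated differ, the reader cannot tell whether the instrument or the elapsed time is responsible.

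**Working it through.** The protocol states no target reliability, SD, retest gap or RCI threshold, so there is no figure of its own to reproduce. All values below are assumptions chosen to show direction and range.

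**1. Systematic shift.** With equal variances, correlation r and a mean shift of d SD between occasions, the absolute-agreement ICC is r / (1 + d²/2).
- d = 0.3: 0.80 / 1.045 = 0.77
- d = 0.5: 0.80 / 1.125 = 0.71

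Pearson's r stays at 0.80 in both cases.

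**2. Differing true change over unequal gaps.** Let the first score have SD 1 and true reliability ρ = 0.80. Let weekly true change have mean m = 0.1 SD and between-person SD s, and let the gap be t weeks, with change and gap unrelated to the starting level. Then

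expected r = ρ / √(1 + m²·Var(t) + s²·(Var(t) + E(t)²)).

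Gaps are fixed at 1 week, uniform on 1–4 weeks (mean 2.5, variance 0.75), or uniform on 1–7 weeks (mean 4, variance 3).

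| s (SD/week) | 1 week | 1–4 weeks | 1–7 weeks |
|---|---|---|---|
| 0 | 0.80 | 0.80 | 0.79 |
| 0.1 | 0.80 | 0.77 | 0.72 |
| 0.2 | 0.78 | 0.70 | 0.60 |
| 0.3 | 0.77 | 0.62 | 0.48 |

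For s = 0.2 and 1–4 weeks: 0.80 / √(1 + 0.0075 + 0.28) = 0.705, and a simulation of this case also gave 0.705. If everyone changes equally, unequal gaps barely matter. If retests are close to weekly, the loss is small. The loss is large only when rates of change differ and gaps are long.

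**3. If such an r entered the RCI.** The cut-off in SD units is 1.96·√(2(1 − r)).
- r = 0.80: 1.24
- r = 0.78 (1 week, s = 0.2): 1.29
- r = 0.705 (1–4 weeks, s = 0.2): 1.51
- r = 0.598 (1–7 weeks, s = 0.2): 1.76

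**4. First-to-last effect size.** At a constant 0.1 SD per week, mean change is 0.1 × mean span.
- All spans 8 weeks: 0.1 × 8 = 0.80 SD
- Spans uniform over 1–8 weeks: 0.1 × 4.5 = 0.45 SD
- Spans uniform over 1–4 weeks: 0.1 × 2.5 = 0.25 SD

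The weekly rate is the same in all three. A growth curve indexed by time targets that rate directly.

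**The case against.** The other side has several good points.

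- **The schedule is not free-floating.** Completion is intended weekly and is prompted by the app and by facilitators. If most retests fall near one week, step 2 gives 0.77 to 0.80 against a true 0.80. A reader might infer that the interval is unconstrained; the text does not support that. What stands is that prompts do not enforce a gap. The protocol itself plans for irregular use: missing weekly data are a primary endpoint, and the interviews sample people who did not complete regularly. Multimedia Appendix 2, which sets item frequency, is not shown and may fix intervals for some item sets.
- **Change does not rest on first versus last alone.** A reader might infer that it does, or that true change contaminates the change analyses. Neither is right: the growth curve is already planned, and true change is what is being estimated. Only the unequal spans remain at issue, and the growth curve does not supply the RCI proportions.
- **An RCI needs no common span.** It asks whether one person's change exceeds measurement error, so unequal spans do not make a person's classification wrong. This stands. The comparison of proportions with the interview RCIs is what suffers.
- **The RCI cut-off may be unaffected.** A reader might infer that it is inflated by about 41% (r falling from 0.8 to 0.6: √(0.4/0.2) = 1.41). That needs long gaps, heterogeneous change and an RCI built on the test-retest r. The text does not say which coefficient is used, and Cronbach alpha is computed in the same section.
- **Pearson and ICC answer different questions.** True, and an ICC of 0.77 lies inside the sampling interval of r = 0.80 at n = 100 (about 0.72 to 0.86). But agreement is the more useful question for a tool that tracks individual scores over time.
- **A condensed article leaves windows to the full plan.** That would excuse silence. Here the statistic and the order-based pairing are stated.

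**Conclusion.** The point holds in a limited form. Followed as written, the test-retest analysis gives a coefficient that is blind to a common shift and mixes measurement error with differing true change over unequal gaps. The downward direction in step 2 assumes that change is unrelated to the starting level. The first-to-last effect sizes and RCIs are not matched in time to the interview RCIs they are to be set beside.

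The size cannot be derived from the document. It ranges from negligible, with near-weekly retests, to substantial, with gaps of several weeks and heterogeneous change.

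The weight is moderate. The objective is secondary and preliminary, no primary endpoint depends on it, and the psychometric endpoint in Table 4 lists internal reliability and validity but neither test-retest reliability nor sensitivity to change. It is still worth correcting, because the results would describe the reliability and responsiveness of a tool proposed for use by services and policy makers.

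**What to change.** - **Reliability.** Make the main test-retest estimate an absolute-agreement ICC with 95% CI, on pairs within a stated window around the item set's intended interval (for example 5–10 days for weekly items). Show Pearson r and all pairs as secondary results, and report the distribution of intervals.
- **RCI input.** Name the reliability coefficient, and do not use a test-retest r taken over all intervals.
- **Sensitivity to change.** Take the time-indexed growth-curve estimate over the 2 months as the main result. Report first-to-last effect sizes and RCIs with their time spans.
- **Comparison with interview RCIs.** Show it also in people with an app completion near 2 months, as a sensitivity analysis only, because that subset is selected on retention.

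The cost is wording, fewer pairs and a slightly wider CI for the main reliability estimate. The window reduces unequal gaps but does not remove the effect of feedback, which should be stated as a limitation.

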#### Smart Track Routine Outcome Monitoring Domains and Items

Consistent with clinical guidelines [3,35] and informed by recommendations arising from systematic reviews evaluating ROM in both mental health [18] and addiction [6] settings, we sought to create a tool that provided multidimensional assessment and feedback. Utilizing an iterative process, we generated a list of candidate outcomes (group attendance; goal setting and attainment; values; self-efficacy; quality of life; self-care; mental health; quantity, frequency, and impact of addictive behavior(s); social support; financial stability; optimism; and frequency, strength, and duration of urges). Corresponding assessment items and/or instruments were then identified to measure these domains. Where possible, validated free-to-access measurement instruments were selected from the published literature. Some changes to the structure, wording, and/or response format were required to improve the clarity and appropriateness of some items. The final item set included in the tool is detailed in Multimedia Appendix 2 [36-47] as a function of the target domain and assessment frequency.

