##### Demographic Characteristics

Collection of sociodemographic characteristics (referral source, date of birth, gender, marital status, indigenous status, education/training, accommodation, and income) will be guided by items from the CSRI [59] and/or NSW minimum data set (MDS) for drug and alcohol treatment services [64].

The Network of Alcohol and other Drug Agencies (NADA) Client Outcome Management System (COMS) was developed by NADA to address the need for greater consistency in how outcomes are assessed across the drug and alcohol treatment sector [46]. We have chosen to use the COMS in this study to ensure that our data are directly comparable with the broader drug and alcohol treatment sectors. The COMS comprises a battery of items designed to assess 4 key domains: (1) drug and alcohol use, (2) psychological health, (3) health and social functioning, and (4) blood-borne virus (BBV) risk. The instruments used to assess each domain are outlined below. The COMS will be administered in full at baseline and at 2-month follow-up. A subset of items (Multimedia Appendix 2) will also be administered via Smart Track.

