###### Client Outcome Management System: Drug and Alcohol Use

####### Severity of Dependence Scale

The Severity of Dependence Scale [65] is a 5-item screening measure of the psychological aspects of dependence that takes less than 1 min to complete. The items assess feelings of impaired control over drug taking, together with preoccupations and anxieties about drug taking. Participants will be asked to respond based on the substance that was causing them the greatest concern (1) over the preceding 2 months and (2) when they began attending SMART Recovery. The items are rated on a 4-point Likert scale, and total scores range from 0 to 15. Higher scores indicate a higher level of dependence. It is widely validated for use across a range of drug types, including heroin, cannabis, cocaine, amphetamine, and benzodiazepines [65-67].

####### Substance Use

Alcohol and tobacco use is measured by assessing both frequency (number of days) and quantity used during the preceding 4 weeks. Furthermore, 2 separate measurements for alcohol are included: number of days the person drank alcohol (and average number of drinks per day) and number of days of heavier drinking than usual (and average number of drinks on those days). For benzodiazepines and any illicit drugs, only the number of days of use is assessed.

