To provide preliminary evidence for participant-reported outcomes in behaviors of concern, recovery, and mental health	Participant-reported progress across the 2-month period of app usage in the following: Addictive behaviors (COMS [41] and item adapted from the Screener for Substance and Behavioral Addictions [42]) Addiction recovery (SURE [43]) Mental health (Kessler [44,68])

^a^COMS: Client Outcome Management System.

^b^SURE: Substance Use Recovery Evaluator.

^c^ROM: routine outcome monitoring.

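### If the app carries days-of-use items, a pooled Pearson correlation cannot separate agreement on any use from agreement on amount; report the two separately for count items

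*Protocol article*

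**What the plan says.** The analysis is in the protocol article, Preliminary Psychometrics of Smart Track ROM Items: "Convergent validity will be examined using Pearson correlation analysis to explore the associations of initial ROM scores with the standardized measures", the measures being the COMS and SURE administered at baseline. The same section assigns Pearson's r to test-retest reliability, comparing the first and second completion of each item set. It adds that, where suitable, internal consistency, test-retest reliability, "concurrent validity, and RCI will be further examined as a function of age group, gender, and primary behavior of concern". Table 4 lists convergent validity of the app's COMS and SURE items as a secondary endpoint.

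The scale of the substance measures is in Client Outcome Management System: Drug and Alcohol Use: "Alcohol and tobacco use is measured by assessing both frequency (number of days) and quantity used during the preceding 4 weeks". It continues: "For benzodiazepines and any illicit drugs, only the number of days of use is assessed".

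On which COMS items are in the app, Demographic Characteristics says: "A subset of items (Multimedia Appendix 2) will also be administered via Smart Track". That appendix is not shown.

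Eligibility admits any adult currently attending a group in New South Wales, with no requirement of current use or of a given substance.

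**The concern.** For any one substance, such a sample mixes people who used it in the recall period with people who did not, either because it was never their problem or because they are abstinent. Non-users plausibly report zero in both app and interview. In a scatter plot they form a cluster at the origin, and the line from that cluster to the cloud of users yields a positive Pearson correlation even if the cloud itself has no slope. The comparison of first and second completion has the same structure.

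At stake is what the coefficient can be said to show. Table 4 also plans to report "Participant-reported progress across the 2-month period of app usage in the following", with addictive behaviors first on the list. Describing change in how much a person uses needs the amount to be measured well, not only the distinction between some use and none. The psychometric section plans no analysis that separates the two.

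**Working it through.** **Inputs.** The documents give no user share, no distribution of days used and no expected correlation, so there is no figure of the plan to reproduce. From the documents come the 4-week day count, the absence of a current-use criterion and the target of 100 participants. The rest is assumed and varied.

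**Model.** Let *p* be the share of users of one substance. Both sources agree on who is a user, and non-users report 0 in both. Among users the amounts have mean *m*, standard deviation *s*, CV = *s*/*m*, and correlation ρ between sources.

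- Covariance: *p*(*m*² + ρ*s*²) − *p*²*m*² = *p m*²[(1 − *p*) + ρCV²]
- Variance in each source: *p*(*m*² + *s*²) − *p*²*m*² = *p m*²[(1 − *p*) + CV²]
- Pooled r = [(1 − *p*) + ρCV²] / [(1 − *p*) + CV²]

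With no agreement on amount (ρ = 0) this is r = (1 − *p*)/[(1 − *p*) + CV²].

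**Illustration.** For days uniform on 1-28, the mean is 14.5 and the variance (28² − 1)/12 = 65.25, so CV² = 65.25/14.5² = 0.310. At 20% users, r = 0.8/(0.8 + 0.310) = 0.72.

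| Share of users | 10% | 20% | 30% | 50% | 80% | 100% |
|---|---|---|---|---|---|---|
| Pooled r, ρ = 0 | 0.74 | 0.72 | 0.69 | 0.62 | 0.39 | 0 |

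Simulation with 100 participants (2000 runs per setting) gave mean pooled r of 0.75, 0.70, 0.62 and 0.39 at 10%, 30%, 50% and 80% users. The mean correlation among users only was between −0.01 and 0.01.

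**How little r distinguishes.** At 20% users, ρ = 0 gives 0.72 and ρ = 0.9 gives (0.8 + 0.9 × 0.310)/1.110 = 0.97. Almost the whole range of agreement on amount is squeezed into 0.72 to 0.97.

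**Sensitivity to the assumptions (ρ = 0).**

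| Change | r at 10% users | r at 50% users |
|---|---|---|
| CV 0.3 | 0.91 | 0.85 |
| CV 0.5 | 0.78 | 0.67 |
| CV 0.8 | 0.58 | 0.44 |
| CV 1.0 | 0.47 | 0.33 |
| App days uniform on 1-7, interview on 1-28 | 0.76 | 0.64 |
| 30% of interview users report zero in the app | 0.62 | 0.47 |
| 10% of users report zero, 5% of non-users report use | 0.55 | 0.53 |

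The last two rows use days uniform on 1-28. Across the spreads tried, r at 10% to 50% users runs from about 0.33 to 0.91.

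**Rank correlation is no remedy.** In the same simulations Spearman's coefficient averaged 0.996, 0.958, 0.854 and 0.480 at 10%, 30%, 50% and 80% users, because the ties at zero dominate it.

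**Precision of a user-only estimate.** With 100 participants and 20% users there are 20 users. By Fisher's transformation, a correlation of 0 among 20 people has a 95% interval of ±tanh(1.96/√17) = ±0.44; among 50 people it is ±tanh(1.96/√47) = ±0.28.

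**The case against.** The strongest objection is that the premise is not in the shown text. Only a subset of COMS items is in the app. The COMS drug and alcohol domain also contains the Severity of Dependence Scale, which is asked about the substance of greatest concern and does not raise this problem. How much and how often a behavior occurs appear in Smart Track Routine Outcome Monitoring Domains and Items only as candidate outcomes, and the wording or response format of some items was changed. This stands: the point is conditional on Multimedia Appendix 2. The candidate list, the COMS subset and the naming of COMS for addictive behaviors in Table 4 make count items likely, and the sponsor can check at once.

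Second, the possible split by primary behavior of concern would remove many people who never used the substance. At the high user shares that could result, the effect is much smaller: 0.39 at 80% users and 0.24 at 90%. This also stands in part. The split is conditional, however, and abstinent members remain in each group.

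Third, ROM items are intended for weekly completion while the interview covers 4 weeks, and the app's recall window is not shown. If the windows differ, zeros are not fully shared, and a difference in days between app and interview has no clear meaning. This stands and shapes the remedy.

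Fourth, Pearson's r is conventional here, the objective is preliminary, and sensitivity to change is assessed separately through effect sizes, the reliable change index and growth curves. That limits the importance. Those analyses describe change in app scores, though, and do not show whether app and interview agree on amount at one time.

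A reader might infer that the planned correlation is spurious, or that the app will wrongly be declared valid for tracking use. The documents support neither: consistent reporting of any use is real convergent evidence, and the protocol sets no threshold for r at which validity would be declared.

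**Conclusion.** The point holds in a limited, conditional form. If the app contains days-of-use or other count items, the planned pooled Pearson correlations, against the interview and between first and second completion, mix agreement on any use with agreement on amount and do not show which is present. The optional split by primary behavior of concern helps only partly.

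The range 0.74 to 0.62 at 10% to 50% users is an example, not a forecast. It rests on perfect agreement on any use, unrelated amounts among users and days uniform on 1-28, none of which comes from the protocol. Unrelated amounts are an extreme case, chosen to show what r cannot detect. The effect shrinks as the share of users rises and vanishes when everyone uses. The Severity of Dependence Scale, K10, quality-of-life and SURE totals are outside the point.

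This is a minor matter in a preliminary secondary objective, but it affects what the study can say about tracking amount of use.

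**What to change.** First confirm from Multimedia Appendix 2 which app items are counts and what period each covers. For those items only, keep Pearson's r if wanted and add:

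1. Agreement on any use versus none: a 2x2 table with percent agreement and kappa.
2. Agreement on amount among users. For first versus second completion, give an intraclass correlation and the mean difference with limits of agreement. For app versus interview, give the same where both cover the same recall window; otherwise give a correlation among users with its confidence interval.

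State in advance whether users are those reporting use in either source or in both; the two coincide in the calculation above only because agreement on any use is assumed perfect. Leave the analyses of the Severity of Dependence Scale, K10, quality-of-life and SURE totals as planned.

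The cost is a few sentences and some extra tables from data already being collected. The drawback is precision: user-only estimates may rest on some 20 people, with an interval of about ±0.44 around a correlation of zero, and should be reported as imprecise.

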#### Secondary Objectives

##### App Engagement and Usage Patterns

A detailed exploration of the relationship between app usage (as indexed by frequency of ROM completion, number of missing items, and time to disengagement) and participant characteristics (demographic, clinical, and treatment variables) will be explored using linear regression. Furthermore, we intend to explore the ROM data graphically to see (1) whether it is likely to characterize particular patterns of usage and (2) whether these patterns appear to be influenced by various participant characteristics. Potential patterns that emerge during this exploratory phase will be followed up using latent trajectory analysis. This will clarify whether app use increases, decreases, or has some other pattern over time. Descriptive statistics will also be used to summarize app-generated data analytics.

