#### Method of Dealing With Missing Data

Descriptive analyses will use all available data. Inferential analyses (eg, linear regression and growth curve modeling) will use multiple imputation (with chained regression equations) as the primary method of dealing with missing data. The number of imputed data sets will depend on the fraction of missing data, but the stability of results will be assessed over a range of imputation numbers.

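### The reliable-change comparison of ROM items with the interview measures lets each side rest on its own participants and its own time span, so a difference need not reflect the instruments

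*Protocol article*

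**What the plan says.** All references are to the Protocol article.

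- **ROM side** (Preliminary Psychometrics of Smart Track ROM Items): "we will calculate RCI between participants’ first and last ROM scores". An effect size is also planned for ROM: "Effect sizes will be estimated for participants’ average ROM change scores between the first and last sessions".
- **Use of the index** (same section): the published criteria "will be applied to describe the proportion of participants who improved, did not change, or deteriorated".
- **Interview side and purpose** (same section): "RCIs will also be calculated for the standardized measures administered at baseline and follow-up to allow comparisons with the ROM items".
- **Analysis set** (Method of Dealing With Missing Data): "Descriptive analyses will use all available data". Imputation is kept for the other kind of analysis: "Inferential analyses (eg, linear regression and growth curve modeling) will use multiple imputation (with chained regression equations) as the primary method".
- **Access to the two data sources:** ROM items are meant to be completed weekly, but "it is up to the individual to decide whether, when, and how they engage with Smart Track" (Overview of the app). Interviews are appointments made by the research team, with reminders by several routes (Data Collection Procedures).

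The article does not say that the comparison is confined to people with both change scores, or that the two intervals are aligned.

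**The concern.** The interview RCIs are there to show whether the ROM items register change as the standardized measures do. That reading requires the same people over the same period. As written, a person with fewer than two completions of an item set drops out of the ROM figure but stays in the interview figure if reached at 2 months. A person with several ROM entries who misses the 2-month interview does the opposite. The ROM interval is whatever lies between a person's first and last entry, while the interview interval is fixed at 2 months.

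The sets are likely to differ. App use is voluntary and interviews are actively pursued. The nested qualitative evaluation also plans 2-month interviews with 10 regular attenders who did not complete the ROM regularly.

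What is at stake is a wrong impression of the ROM items' sensitivity to change, in either direction. No primary endpoint depends on it.

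**Working it through.** **1. Who contributes, and over what period**

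| | ROM RCI | Interview RCI |
|---|---|---|
| Needs | at least two completions | baseline and 2-month interview |
| Interval | first to last entry, any length | 2 months |
| Missing data | descriptive, so all available | descriptive, so all available |

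The RCI is used to describe proportions, and neither it nor the effect size is among the examples given for imputation. The natural reading is therefore that nothing brings the two sets together.

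**2. Size of the participant mismatch**

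The plan states no figure for this comparison, so there is none to reproduce. The inputs below are assumptions, and both instruments are made equally sensitive:

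- true change: mean 0.2 SD, SD 0.7
- reliability 0.85 for both instruments
- 80% interviewed at 2 months, with follow-up correlated 0.2 with true change
- the share with at least two ROM completions, and its correlation with true change, varied

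Cut-off:

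- SEM = √(1 − 0.85) = 0.387
- SD of a difference due to error = √2 × 0.387 = 0.548
- reliable improvement means observed change above 1.96 × 0.548 = 1.074

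With no selection, observed change has SD √(0.7² + 0.548²) = 0.889. The proportion improved is P(Z > (1.074 − 0.2)/0.889) = P(Z > 0.98), or 16.3%.

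Simulated percent reliably improved, each instrument on its own available data:

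| Repeat completers | Correlation with change | ROM | Interview | Difference (points) |
|---|---|---|---|---|
| 60% | 0 | 16.3 | 17.5 | −1.2 |
| 60% | 0.3 | 19.9 | 17.5 | +2.4 |
| 60% | 0.5 | 22.2 | 17.6 | +4.6 |
| 40% | 0.3 | 22.1 | 17.5 | +4.6 |

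In participants with both change scores the two instruments agree to within about 0.2 points in each case (about 21.3% on both in the second row). The negative sign in the first row arises only because interview follow-up was itself assumed to be related to change.

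A second model assumed mean change 0.4, SD 0.8, reliability 0.8, and interview follow-up unrelated to change. It gave 0 points when app use was unrelated to change. It gave about 4 points with 60% completers and a log-odds ratio of 0.5 per SD of change (24.7% v 20.5%). It gave about 12 points in its most extreme case, 40% completers and a log-odds ratio of 1.0 (32.4% v 20.5%).

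**3. The interval mismatch**

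Let change be linear and let the last ROM entry fall anywhere from week 1 to month 2. With 60% completers and correlation 0.3 in the first model, the common set then shows 10.6% on ROM against 21.3% on interview for identical instruments. The second model, with no link between app use and change, gives 10.4% against 20.6%. Restricting to common participants does not remove this.

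**4. Precision at the target of 100 participants** (first model)

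| Repeat completers, correlation | Total error, own sets | Total error, common set |
|---|---|---|
| 60%, 0 | 5.6 | 6.1 |
| 60%, 0.3 | √(2.4² + 5.6²) = 6.1 | 6.6 |
| 60%, 0.5 | 7.5 | 6.8 |
| 40%, 0.3 | 8.2 | 8.4 |

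Total error is the root mean square error of the difference, in points. In the second row the common set has about 49 people, its bias is near 0, and the SD of the difference rises from about 5.6 to about 6.6. For the paired difference in mean change, the common set removes the bias with no loss of precision.

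**The case against.** The strongest reply has four parts.

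**The bias needs a link that the plan does not assert.** A reader might infer that the authors expect people to disengage, and to do so according to clinical characteristics. The section on app engagement does not say that. It indexes usage by "frequency of ROM completion, number of missing items, and time to disengagement" and will explore whether usage relates to participant characteristics. A link with baseline characteristics would also not by itself be a link with later change. This stands: both size and direction rest on assumptions.

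**Mean change is not the planned contrast.** Under the assumptions above one could quote mean change of 0.33 SD on ROM against 0.25 SD on interview, about one third larger. But an effect size is planned for ROM only. The comparison named in the text is of RCIs, so the percentages are the relevant figures. For the same reason the growth curve model, though imputed, adds nothing here: it is not set against an interview measure.

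**At 100 participants the distortion is modest beside sampling error, and the common set costs precision.** This stands too. In three of the four cases the total error of the RCI contrast is slightly larger in the common set. The argument for the common set is that its error is not systematic and its comparison is interpretable, not that it is always closer to the truth.

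**A matched comparison is compatible with the text, and an article may leave such detail to a fuller document.** It is true that nothing forbids a matched comparison. But the article itself states the comparison, its purpose and the analysis-set rule, and read together these lead to unmatched sets. The point concerns what is stated, not what is left out.

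**Conclusion.** The point holds as a minor one. As written, the comparison can confuse a difference between instruments with a difference in participants or in length of observation.

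In the four tabled cases the participant mismatch amounts to about −1 to +5 points in percent reliably improved. More extreme assumptions give more, and no relation of app use or follow-up to change gives none. The interval mismatch can be larger, roughly halving the ROM figure if last entries are spread evenly over the 2 months and change is linear. All of these sizes rest on assumed usage, follow-up and change.

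A reader might go further and conclude that the ROM items will look too sensitive. The documents do not support that: the participant mismatch can go either way, and short ROM intervals would push in the opposite direction. Nor does the point touch feasibility, acceptability or the separate descriptive RCIs. It affects one comparison within a secondary objective that is offered as preliminary.

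**What to change.** In the section on preliminary psychometrics:

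1. Make the ROM-versus-interview comparison only in participants who have both change scores.
2. For that comparison, take the ROM completions closest in date to the baseline and 2-month interviews, within a window stated in advance, in place of first and last.
3. Analyse it as paired data: cross-tabulate the RCI categories on the two instruments and report the within-person difference in standardized change.
4. Report the all-available RCI figures for each instrument separately, each with its n and the length of the ROM interval, and do not compare them across instruments.

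This takes a few sentences and a filter in the code, with no new data. The cost is a smaller set (about 49 of 100 under the 60% completer, correlation 0.3 assumptions, and fewer once the window applies) and a somewhat less precise RCI contrast. The common set alone, without matched dates, would not be enough.
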